### Data analytic plan

#### Primary hypothesis

*Participants who receive the culturally tailored narrative film intervention will demonstrate greater behavioral intent to call 911 for suspected stroke, as measured by the STAT at immediate post-intervention, 6 months and 1 year following the intervention compared to those in the usual care arm.* The change from pre- to post-intervention values of continuous outcomes (STAT scores) will be modeled as functions of treatment group, time, and the interaction of time and treatment. The primary test concerns the Group × Time interaction, and the resulting F-test will provide the primary “intent-to-treat” test of the hypothesis. The magnitude of the treatment effect, with 95% CI, for STAT scores will be estimated. Design effects of clustering within churches and repeated measures together with unreliability, serial correlations and possible heterogeneous variances will be modeled when necessary.

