### Study measures

#### Behavioral intent to call 911

The primary outcome will be self-reported behavioral intent to call 911 based on the validated STAT instrument [56]. This measure reliably predicts the actions that respondents would take if a stroke occurs and serves as our measure of stroke literacy. Most stroke knowledge assessments use either recall tasks (spontaneously naming stroke symptoms) or recognition tasks (selecting the correct stroke symptoms from a list), but the situation of acute stroke is different. During an acute stroke situation, symptoms are *experienced* or *observed.* The identification of symptoms is meaningless if it does not lead to urgent action. Knowing to call 911 when a stroke diagnosis is provided is not the same as calling 911 when stroke symptoms present.

The STAT measures behavioral intent to call 911 for suspected stroke symptoms using hypothetical stroke scenarios in which the stroke diagnosis is not provided. Each scenario features one of the cardinal stroke symptoms or a distracter symptom, and respondents are asked how they would respond to the scenario. The five cardinal signs of stroke include weakness, speech impairment, vision impairment, headache and dizziness [57]. The 21 scenarios are derived from these 5 cardinal “suddens” stroke symptoms. There are 21 because the 5 cardinal symptoms are presented in a variety of situations. All participants in the intervention and control conditions will be administered the STAT at baseline and the 6-month and 1-year follow-ups.

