### Sample size and power analysis

#### Power calculations for the primary outcome (behavioral intent to call 911 using the stroke action test)

Power calculations were based on both examination of endpoint differences and on rates of change over time using data from all three waves of data collection. The main calculation shown in Table 1 is for the primary analysis examining rate of change. The outcome is treated continuously, and we assumed a two-tailed test with α = 0.05 and 1-β = 0.80. The following assumptions, based on the literature on stroke literacy and stroke action using the STAT [56], were used to calculate sample size and power: R =0.85 (reliability); g = 2 (group); σ = 17.83 (pooled SD of examinee subgroups); δ = 8, 9, 10 (Stroke Action point reduction); d = δ/σ where δ is the endpoint mean differences, and d is Cohen’s d (0.45, 0.50, 0.56). The number of churches posited to be economically feasible is 7 per arm, and the cluster size is 18, with over-recruitment to 25. The ICC derived from data from over 30 churches participating in a separate, ongoing randomized trial of a church-based intervention was posited to be 0.02. Thus, the VIF = 1+ (clustersize-1)*ICC = 1.34. It was assumed that ρ = 0.6 (the average correlation between baseline and follow-up).

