### Secondary hypothesis

*Participants who receive the culturally tailored narrative film intervention will demonstrate greater stroke symptom recognition at 6 months and 1 year following the intervention compared to those in the usual care arm.* Binary outcomes (stroke symptom knowledge) will be examined using generalized estimating equations (GEEs) with a logit link. Because randomization is at the church level, with clustering, such models allow for modeling the correlation due to clustering and repeated measures. Stroke knowledge will be coded as knowledgeable or not, based on predetermined cut scores. Baseline knowledge will be included in the model. Results can be converted to odds ratios. In the event that the above described logit analyses indicate one or more sources of potential bias, the predicted values of those analyses will be included as covariates in the a multilevel logistic regression model (SAS, version 9).

Prior to analyses, baseline values of all variables from each arm will be examined; however, no *p* values will be provided, and covariates are not proposed for inclusion in the main analyses of treatment effects. If one or more sources of potential (selection or attrition) bias are identified, the predicted values from those analyses will be included as covariates in secondary analyses. Depending on the severity of missing data, other modeling techniques may be used.

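### The primary STAT analysis uses baseline only by subtraction, which is less efficient for baseline-to-follow-up contrasts than baseline adjustment and does not match the variance that reproduces Table 1

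*Protocol article*

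**What the plan says.** Under Primary hypothesis, the protocol article sets out the model: "The change from pre- to post-intervention values of continuous outcomes (STAT scores) will be modeled as functions of treatment group, time, and the interaction" (treatment by time). The Group × Time interaction is the primary test. No baseline STAT term is listed.

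Under Secondary hypothesis, a sentence that refers to the main analyses generally says that "covariates are not proposed for inclusion in the main analyses of treatment effects". Covariates appear only in secondary analyses, as predicted values, if selection or attrition bias is found. For the binary knowledge outcome, the same section says: "Baseline knowledge will be included in the model".

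Under Study measures, participants in both arms are "administered the STAT at baseline and the 6-month and 1-year follow-ups". The primary power calculation gives the strength of the link between baseline and later scores: "It was assumed that ρ = 0.6 (the average correlation between baseline and follow-up"). The section on power for rate of change describes three time points with baseline as one of them, a Time × Group mixed model, more than 80% power for 8 points with 125 per group, and detection of effects of about 6 points.

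**The concern.** A change score gives baseline a fixed slope of 1. With a correlation of 0.6 and equal variances, the slope that minimises variance is 0.6. The change score therefore over-corrects and carries more variance than an analysis with baseline as a covariate. A three-wave mixed model in which each arm has its own free baseline mean has the same weakness, because its Group × Time contrasts are again differences of changes.

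What is at stake is power on the primary endpoint, lost although the needed measurement is already collected, and agreement between the stated analysis and the sample size. The over-correction can also be seen in a single trial: a chance baseline difference between arms of 7 churches leaves part of itself, with reversed sign, in the estimated effect.

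**Working it through.** **Inputs** (protocol article, power section for the primary outcome): two-sided α = 0.05 and 80% power; SD σ = 17.83; reliability R = 0.85; ρ = 0.6; VIF = 1 + 17 × 0.02 = 1.34. From Table 1 and the section on rate of change: 125 per arm, effects of 8, 6.34 and about 6 points.

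**Step 1: reproduce Table 1.** Use n = 2(1.96 + 0.842)² σ² f / δ², where 2(1.96 + 0.842)² σ² ≈ 4,990, and solve for δ in the lower row.

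| Variance factor f | n at δ = 8 / 9 / 10 | detectable δ at n = 75 / 100 / 125 |
|---|---|---|
| Table 1 as printed | 79 / 62 / 50 | 8.19 / 7.10 / 6.34 |
| Baseline-adjusted: (1−ρ²) × VIF / R = 0.64 × 1.34 / 0.85 = 1.009 | 78.7 / 62.2 / 50.4 | 8.19 / 7.10 / 6.35 |
| Change score: 2(1−ρ) × VIF / R = 0.80 × 1.34 / 0.85 = 1.261 | 98.3 / 77.7 / 62.9 | 9.16 / 7.93 / 7.10 |
| f = 1 (no ρ, VIF or R) | 78.0 / 61.6 / 49.9 | 8.16 / 7.06 / 6.32 |

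The adjusted factor reproduces the table to within rounding. The change-score factor, which is also the slope factor for three equally spaced waves, does not. A factor of 1 comes close, but only by dropping every stated design input, and it fits the lower row less well.

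**Step 2: power for a single follow-up, 125 per arm.** Var = 2 × 17.83² × 1.34 × k / (0.85 × 125) = 8.02k. For the change score k = 0.80 and SE = 2.53; for the adjusted analysis k = 0.64 and SE = 2.27. The variance ratio is 1.25 and the SE ratio √1.25 = 1.118. Power = Φ(δ/SE − 1.96):

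| δ | Change score | Baseline-adjusted |
|---|---|---|
| 6 | 65.9% | 75.4% |
| 6.34 | 70.6% | 79.9% |
| 8 | 88.5% | 94.2% |

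The effect detectable with 80% power is 7.10 against 6.35 points. The gain is 3.3 points of power at δ = 9 and 1.6 at δ = 10. Across ρ from 0.4 to 0.8 it runs from 15.2 down to 1.9 points at δ = 6.34, and from 13.7 down to 0.3 at δ = 8.

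**Step 3: three-wave Group × Time test, 2 df.** Assumptions not in the article: correlation 0.6 between every pair of waves, and the same effect at both follow-ups. The two changes have variance 0.80 and covariance 0.6 + 1 − 1.2 = 0.40, so the noncentrality is δ² × 2/(0.80 + 0.40) / 8.02. After adjustment, the variance is 0.64 and the covariance 0.6 − 0.36 = 0.24, which gives δ² × 2/(0.64 + 0.24) / 8.02. Power is 68.7% against 82.4% at 6 points, 73.7% against 86.5% at 6.34, and 91.5% against 97.5% at 8.

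**Step 4: a contrast only between the follow-ups.** If the outcomes are the 6-month and 1-year changes, Group × Time compares (Y12 − Y0) − (Y6 − Y0) = Y12 − Y6. Baseline cancels. With equal correlations the factor is 2(1−0.6) = 0.80 with or without adjustment.

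**Step 5: chance imbalance.** The SD of the between-arm baseline difference is 17.83 × √(2 × 1.34/125) = 2.61 points, or 2.61/√0.85 = 2.83 if R is applied as in the SEs above. The change score retains −(1−ρ) = −0.4 of any such difference: 1.04 points per SD (1.13 with R).

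**The case against.** - **On the literal model the gain may be nil.** If the Group × Time test compares the two follow-up changes, step 4 shows that adjustment makes no difference. This stands. A reader might infer that baseline adjustment helps every contrast; it does not. The loss applies to baseline-to-follow-up contrasts, and these remain relevant because the article counts baseline among the three waves behind its power claim.
- **The no-covariates sentence may not mean the outcome's own baseline.** The same section admits baseline knowledge to the secondary model, so the authors may reserve the word covariate for other variables. That is possible, but the primary model as listed still has no baseline term. The contrast with the secondary model is only suggestive, since subtraction is not an option in a logit GEE.
- **Table 1 suggests that the authors had baseline conditioning in mind.** It may. In that case the stated model and the sample size disagree, and the text still needs correcting.
- **Imbalance.** A reader might infer that raw baseline imbalance stays in the estimate, or that this is a second harm. Neither is supported. About 40% remains, with reversed sign; it is error conditional on the observed imbalance and not bias over repeated randomisation. It is also the same quantity as the variance loss: 0.80 − 0.64 = (1−ρ)² = 0.16.
- **The size of the loss is conditional.** It depends on ρ and on the effect assumed, and the headline power claim at 8 points is met either way. This stands.

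**Conclusion.** The point holds for contrasts between baseline and follow-up, including a three-wave Group × Time test with unconstrained baseline means. On the plan's inputs and a single follow-up, the stated analysis gives up 5.7 points of power at 8 points, 9.3 at 6.34 and 9.6 at 6. These figures use the normal approximation and apply the same VIF to both analyses. With a t reference on 12 df, single-follow-up power at 6.34 points is 63.3% against 72.9%.

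The stated analysis does not match the variance that reproduces Table 1. A reader might infer that the trial is underpowered for its main target; the figures do not support that, since power at 8 points is 88.5% with change scores. What fails is the claim for about 6 points, which stays below 80% under a single-follow-up or 2-df change-score test. Adjustment takes the 2-df test above 80% at 6 points (82.4%, under the assumptions of step 3), but not the single-follow-up test (75.4%).

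**What to change.** Under Primary hypothesis, take the 6-month and 1-year STAT scores as outcomes, with baseline STAT and its interaction with time as prespecified covariates, and keep the church clustering. Test the group effect at the follow-ups, either jointly (group main effect and group × time) or as one named follow-up contrast. Adding baseline while testing only the change between 6 months and 1 year would bring no gain under equal correlations.

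Under Secondary hypothesis, change the sentence on covariates to say that none are proposed other than the baseline value of the outcome.

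Prefer covariate adjustment to a longitudinal model that forces a common baseline mean. Participants are recruited after their church has been randomised, so equal baseline means in the two arms cannot be assumed. Report the change-score result as a sensitivity analysis.

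The cost is wording in the analysis plan and the extra baseline terms in the model. No new data, visits or participants are needed.

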### Secondary hypothesis

*Participants who receive the culturally tailored narrative film intervention will demonstrate greater stroke symptom recognition at 6 months and 1 year following the intervention compared to those in the usual care arm.* Binary outcomes (stroke symptom knowledge) will be examined using generalized estimating equations (GEEs) with a logit link. Because randomization is at the church level, with clustering, such models allow for modeling the correlation due to clustering and repeated measures. Stroke knowledge will be coded as knowledgeable or not, based on predetermined cut scores. Baseline knowledge will be included in the model. Results can be converted to odds ratios. In the event that the above described logit analyses indicate one or more sources of potential bias, the predicted values of those analyses will be included as covariates in the a multilevel logistic regression model (SAS, version 9).

Prior to analyses, baseline values of all variables from each arm will be examined; however, no *p* values will be provided, and covariates are not proposed for inclusion in the main analyses of treatment effects. If one or more sources of potential (selection or attrition) bias are identified, the predicted values from those analyses will be included as covariates in secondary analyses. Depending on the severity of missing data, other modeling techniques may be used.

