### Stroke knowledge

Following the STAT survey, we will directly assess knowledge of the five cardinal “suddens” stroke symptoms, which we will present in a multiple-choice format alongside seven distracter symptoms derived from the STAT. A composite score will be calculated by counting the number of correct responses to the five stroke symptoms [57] and seven distracter symptoms (maximum score = 12), modeled after the Behavioral Risk Factor Surveillance System (BRFSS) [58]. Participants will be administered the stroke knowledge battery at baseline and the 6-month and 1-year follow-ups.

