### Power calculation for the secondary outcome (stroke symptom knowledge)

For this binary outcome, it is posited that the control group will improve by 6%, starting at 4% with knowledge, based on a composite score for correct answers to the five cardinal “suddens” symptoms [57]. Given randomization, the intervention group is posited to start at the same level and improve 24%, for a net improvement of 18%. The assumptions are: R =0.85 (reliability); g = 2 (group); cluster size = 18; ICC = 0.02; VIF = 1+ (clustersize-1)*ICC = 1.34. A sample size of 125 subjects per group will provide 80% power to detect a group difference in the rate of increased knowledge at 6 months, from a baseline rate of 4% to a desired level of 28%.

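### Stroke knowledge is measured on twelve items but powered on a five-symptom composite, and the analysis does not say which score is cut; a graded count on one named item set should be the main analysis.

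*Protocol article*

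**What the plan says.** Three sections of the protocol article describe the secondary outcome.

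- **Stroke knowledge (Study measures).** "A composite score will be calculated by counting the number of correct responses to the five stroke symptoms", together with "seven distracter symptoms (maximum score = 12". It is collected at baseline, 6 months and 1 year.
- **Power calculation for the secondary outcome.** The outcome is binary. The control arm is assumed to be "starting at 4% with knowledge, based on a composite score for correct answers to the five cardinal" symptoms, and to gain 6 points. The intervention arm starts at the same level and gains 24 points. Distracters are not mentioned. With 125 per group, cluster size 18, ICC 0.02, VIF 1.34 and R = 0.85, the stated power is 80%.
- **Secondary hypothesis (Data analytic plan).** "Binary outcomes (stroke symptom knowledge) will be examined using generalized estimating equations (GEEs) with a logit link", and "Stroke knowledge will be coded as knowledgeable or not, based on predetermined cut scores". The section does not say whether the twelve-item or the five-symptom score is cut. Baseline knowledge enters the model. No analysis of the 0-12 count itself is described.

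**The concern.** As described, the outcome that is measured and the outcome that is powered rest on different items, and the analysis section does not say which one it uses.

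The difference is more than wording. Suppose that rejecting a distracter is the correct response. A participant who endorses every item then scores 5 of 5 on the five-symptom composite but 5 of 12 on the composite in the measures section. An intervention that made people label more complaints of any kind as stroke would raise the first score and could lower the second. The two definitions could therefore point in opposite directions on the trial's secondary hypothesis. If the choice were still open once data were seen, it could decide the result.

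Two further matters follow. The rates used for power belong to one of the two scores and say nothing about the pass rate on the other. And a graded score, already computed at every wave, is reduced to pass or fail for its only described analysis.

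**Working it through.** **Inputs from the article.** 6-month rates p1 = 0.04 + 0.06 = 0.10 and p2 = 0.04 + 0.24 = 0.28; n = 125 per group; VIF = 1 + 17 × 0.02 = 1.34; R = 0.85. The two-sided α of 0.05 is stated for the primary outcome and assumed here for the secondary. The way R was applied is not stated, so variants are shown.

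**Step 1: reproduce the 80%.** Two-proportion test with pooled variance under the null:

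power = Φ{[(p2 − p1) − 1.96·√(2p̄(1 − p̄)/n_e)] / √([p1(1 − p1) + p2(1 − p2)]/n_e)}, with p̄ = 0.19.

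- VIF only: n_e = 125/1.34 = 93.3. Power = Φ{(0.18 − 1.96 × 0.0574)/0.0559} = Φ(1.206) = 88.6%.
- VIF, with n also multiplied by R: n_e = 93.3 × 0.85 = 79.3. Power = Φ{(0.18 − 1.96 × 0.0623)/0.0606} = Φ(0.955) = 83.0%.
- VIF, with the difference multiplied by R instead (0.18 × 0.85 = 0.153): 78.7%.

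The stated 80% is attainable for a binary outcome at these rates.

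**Step 2: what if the cut is on the 0-12 score?** The article gives no pass rate for that score, so the control rates below, other than 10%, are assumptions. The 18-point difference is kept.

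| Control rate at 6 months | Power, VIF only | Power, VIF and R on n |
|---|---|---|
| 5% | 95% | 91% |
| 10% (article, five symptoms) | 89% | 83% |
| 20% | 78% | 71% |
| 30% | 72% | 64% |
| 40% | 69% | 62% |

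Power can move either way. A stricter cut raises it, and a cut that more people pass lowers it to about 62-78%.

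**Step 3: cost of a cut.** For a normal score with a proportion p above the cut, the efficiency of the dichotomy relative to the full score is φ(z_p)²/[p(1 − p)].

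- p = 0.10: 0.1755²/0.09 = 0.34
- p = 0.19: 0.2714²/0.1539 = 0.48
- p = 0.28: 0.3366²/0.2016 = 0.56
- p = 0.50: 0.3989²/0.25 = 0.64

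The loss is therefore 36-66%, and only if the score is roughly normal.

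**Step 4: does a graded count help on the actual item sets?** Illustration with independent items, knowledgeable taken as all five symptoms correct, 80% power, and no inflation for clustering. Per-item accuracy is 0.10^(1/5) = 0.631 against 0.28^(1/5) = 0.775. The mean difference is 5 × (0.7752 − 0.6310) = 0.721 items. The two variances sum to 5 × 0.631 × 0.369 + 5 × 0.775 × 0.225 = 2.04.

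- Five-symptom dichotomy: about 73 per arm.
- Five-symptom count: 7.85 × 2.04/0.721² = about 31 per arm.
- 0-12 count, no effect on distracters: each arm's variance gains 7a(1 − a), where a is distracter accuracy. At a = 0.90: 7.85 × (2.04 + 1.26)/0.721² = about 50 per arm. At a = 0.50: 7.85 × (2.04 + 3.50)/0.721² = about 83.
- 0-12 count with a 0.1 correlation among distracters (distracter variance × 1.6): about 85 per arm at a = 0.80 and 115 at a = 0.50.

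Grading the same items that are cut is clearly more efficient. Adding seven items that the film does not affect can use up that gain.

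**The case against.** **Power and analysis are both binary.** This stands. A reader might infer that dichotomising is itself what breaks the power calculation. It is not: both sections treat the outcome as binary, and step 1 shows that the 80% is reachable on its own inputs. The mismatch lies in the item set and in the unnamed score.

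**Five symptoms may be shorthand.** The power section does not say that distracters are excluded, and both sections speak of a composite score. This is possible, but one section spells out seven distracters and a maximum of 12 while the other names only the five symptoms, and nothing links the article's rates to the twelve-item score.

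**Cut values belong in an analysis plan.** Agreed. The article calls them predetermined, and their absence is not the point. What needs settling is which score they apply to.

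**About half the information is lost.** A reader might infer this from a pass rate near 19%. The documents do not support it as a fixed figure. It needs a roughly normal score, and it borrows pass rates from the five-symptom outcome for a different, bounded 13-level score.

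**Baseline adjustment is fragile.** At 4%, only 125 × 0.04 = 5 people per arm would be knowledgeable at baseline, so a reader might expect an unstable model. The article says only that baseline knowledge is included, not that it enters as a binary variable, so this cannot be held against it.

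**Moving to the 0-12 mean may not help.** This stands in part. Step 4 gives about 50-115 per arm for that score against 73 for the five-symptom dichotomy if the film leaves the distracters unchanged. It argues for choosing the item set first, not against a graded analysis.

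**Conclusion.** The concern holds as an inconsistency of definition with a consequence for power. The measures section and the power section describe different item sets, and the analysis section does not choose between them. The 80% may stand for a five-symptom binary outcome (83-89% with VIF, with or without R applied to n). It is not established for a cut on the 0-12 score, where assumed control rates of 20-40% and an unchanged 18-point difference give about 62-78%.

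The dichotomy is a separate, milder matter of efficiency: relative efficiency 0.34-0.64 under normality, or about 31 against 73 per arm for the five-symptom count under independent items and an all-correct rule. These sizes rest on my assumptions. The plan is not shown to be underpowered on its own inputs.

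**What to change.** 1. Choose one item set and state it identically in the measures, power and secondary-hypothesis sections, naming the score to which the cut applies.
2. Label the 4%/10%/28% calculation as belonging to the five-symptom binary outcome.
3. Make the graded count on the chosen items the main analysis of the secondary hypothesis: adjusted for baseline score, allowing for church clustering, at 6 and 12 months. Keep the knowledgeable proportion by GEE, with its cut stated, as supportive.
4. If the twelve-item score is chosen, also report the five-symptom and distracter counts separately, because distracters can dilute an effect on symptom recognition.

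The cost is wording only, since the items are already collected at all three waves. There are two downsides. A mean difference in items is less intuitive than a percentage, which is why the percentage is kept. The graded analysis also has no stated power calculation, and the revised text should say so or supply one.
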